## **7. Statistical Analysis and Sample Size Calculation**

For the primary analysis, we will perform linear regression, adjusted for sex (clinical stratification factor) and intraoperative opioid MME to assess the comparison between trial groups, with a P-value threshold of 0.05 being considered significant. If residuals indicate substantial violations of the linear regression assumptions, alternate methods will be attempted, such as analyzing log-transformed data, using bootstrap hypothesis testing or two-sample t-tests without equal variance. A modified intention-to-treat analysis will be employed, including only patients in whom a block catheter was placed, and a dose of study drug was administered. The time-to-event outcomes will be modelled simultaneously using a multistate framework. This approach will handle competing risks, such as death, and treat other non-fatal events, that could be related to each other, as intercurrent events. Sensitivity analyses using complete intention-to-treat and per protocol populations will also be conducted. Categorical data will be summarized by frequencies and percentages, and continuous variables by means and standard deviations (plus medians and interquartile ranges for non-symmetric data).

In order to detect a mean difference of 10 MMEs, assuming a standard deviation of 25 and an alpha value of 0.05, a sample size of 133 participants per group would be required to provide a power of 90%. Assuming an attrition rate of 25%, approximately 340 patients will need to be randomized for the primary modified intention-to-treat analysis.

Pre-specified subgroup analyses of the primary outcome include:

- Age
- Race/Ethnicity
- Sex/Gender
- Diabetes status
- BMI
- Type of operation
- Site

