The analysis of covariance (ANCOVA) model with a fixed effects for treatment group, sex, BMI and intraoperative MMEs ( $<$ median,  $\geq$ median) will be used to analyze the primary efficacy endpoint. The least squares (LS) mean, standard errors, and 2-sided 95% confidence intervals (CIs) for each treatment group and for the mean difference compared to placebo will be estimated. The model will be fit assuming unequal variances for each treatment group. If substantial deviations from the model assumptions are observed, then supportive analyses, such as robust regression, non-parametric analyses, etc. will be considered. Missing values of predictors will either be imputed by the overall mean or most frequent category.

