### 3.4.2 Secondary Efficacy Endpoints

Pain score during the 72 hours following catheter insertion will be analyzed by a mixed model for repeated measures (MMRM), with random effects for intercept and time, fixed effects for treatment, sex, and intraoperative MMEs (<median, ≥median), and an unstructured covariance matrix.

The analysis of cumulative postoperative opioid use measured as MMEs from catheter insertion until discharge from hospital will be by the same methods as for the primary efficacy endpoint, including the joint model sensitivity analysis.

The analysis of incidence of delirium during the 72 hours following catheter insertion will be by logistic regression with fixed effects for treatment group, sex, and intraoperative MME (<median, ≥median). The treatment odds ratio (OR) and associated 95% confidence interval will be provided.

The analysis of Quality of Recovery-15 Scale administered 24-96 hours post-surgery will be by the same methods as for the primary efficacy endpoint.

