### 3.4.3 Exploratory Efficacy Endpoints

The analyses of time-to-event exploratory efficacy endpoints will be by proportional hazards models with fixed effects for treatment, sex, and intraoperative MMEs (<median, ≥median). The treatment hazard ratio (HR) and associated 95% CI will be provided. A cause-specific approach for competing terminal events (i.e., deaths) will be applied by censoring participants at the time of death. Cumulative incidences by treatment group will be estimated by Kaplan-Meier methods.

The analyses of incidence of postoperative nausea or vomiting will be by the same methods as pain score or delirium.

Opioid requirements post-discharge will be summarized by descriptive statistics.

The analyses of chronic post sternotomy pain/disability and patient reported outcomes assessed with the McGill Pain Questionnaire (3 months) and PROMIS 29 score (6 weeks, 3 months) will be by the same methods as for the primary efficacy endpoint.

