### 3.4.4 Subgroup Analysis

The primary efficacy endpoint will be analyzed by the following subgroups:

- Age (<median, ≥median)
- Race/ethnicity
- Sex (male, female)
- Diabetes status
- BMI (<median, ≥median)
- Type of Operation
- Intraoperative MMEs (<median, ≥median)

An ANCOVA model with a fixed effects for the treatment group, sex, intraoperative MMEs, subgroup (not applicable for sex and intraoperative MMEs subgroup analyses) and the interaction between treatment group and subgroup will be applied. The least squares (LS)

mean, standard errors, and 2-sided 95% confidence intervals for each treatment group and for the mean difference compared to placebo, within each level of the subgroup, will be estimated.

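### Outside the subgroup analyses, no primary, secondary or exploratory efficacy model adjusts for age; adding it before unblinding is a near-costless chance of extra precision

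*Combined protocol and SAP*

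**What the plan says.** The primary analysis (SAP 3.4.1) is "The analysis of covariance (ANCOVA) model with a fixed effects for treatment group, sex, BMI and intraoperative MMEs", with intraoperative MME split at the median. Protocol section 7 has a shorter list: "we will perform linear regression, adjusted for sex (clinical stratification factor) and intraoperative opioid MME".

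The other efficacy models are:

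- Pain score (SAP 3.4.2): "fixed effects for treatment, sex, and intraoperative MMEs (<median, ≥median), and an unstructured covariance matrix".
- Delirium (SAP 3.4.2): "logistic regression with fixed effects for treatment group, sex, and intraoperative MME".
- Time-to-event endpoints (SAP 3.4.3): "proportional hazards models with fixed effects for treatment, sex, and intraoperative MMEs (<median, ≥median", with the bracket closing after the median split.
- Opioid use to discharge, QoR-15, McGill and PROMIS-29 follow the primary method.
- Nausea and vomiting follow the pain or delirium method.

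None of these contains age. SAP 3.3.3 lists age among the baseline characteristics. SAP 3.4.4 names it as a subgroup factor, "Age (<median, ≥median"). In that section the model also contains "subgroup (not applicable for sex and intraoperative MMEs subgroup analyses) and the interaction between treatment group and subgroup will be applied", so a dichotomised age term does enter one analysis of the primary endpoint. Type of operation is a subgroup factor in both documents, but its levels are not given and it is not named in the SAP 3.3.3 list. Protocol 3.5 stratifies randomisation by site and sex only.

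**The concern.** The SAP already adjusts for factors chosen for their likely relation to opioid use rather than because they were stratified on: intraoperative MME, and BMI, which the SAP adds to the protocol's list. Age is available for the same purpose and is left out of the headline model. If older and younger patients differ in 72-hour opioid use, that variation stays in the residual and the primary confidence interval is wider than it needs to be. Age is not a stratification factor either, so a chance age difference between arms is neither limited by the design nor conditioned on in the analysis. At stake is the width of the interval and a modest amount of power, not the validity of the test.

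**Working it through.** **Inputs.** From SAP 2.2.2: difference 10 MME, SD 25, two-sided alpha 0.05, 133 per group (266 in total), power 90%. The share R² of residual variance that age explains, beyond sex, BMI and intraoperative MME, is not in the documents. It is assumed over 2% to 10%. SD 25 is taken as the residual SD of the planned model.

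**Step 1: reproduce the plan's figure.** The normal approximation gives n = 2 × (1.960 + 1.282)² × 25² / 10² = 131.3, so 132 per group. The two-sample t calculation gives 133, with power 90.1%. The stated figure reproduces. The standard error at 133 per group is 25 × √(2/133) = 3.07 MME.

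**Step 2: effect of a prognostic covariate.** Residual SD becomes 25 × √(1 − R²), and the standard error scales by √(1 − R²). Power comes from the noncentral t with that SD at 133 per group.

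**Step 3: cost of the covariate.** Fitting q extra terms that explain nothing widens the standard error by about √[263/(263 − q)], where 263 = 266 − 3. The baseline terms already in the model are ignored here, which hardly changes the ratio.

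- Age alone, q = 1: √(263/262) = 1.0019, or 0.2% wider. Break-even R² = 1 − 262/263 = 0.4%.
- Age plus a few operation categories, q = 4 or 5 (assumed): √(263/259) = 1.0077 and √(263/258) = 1.0096, or 0.8% to 1.0% wider. Break-even R² is 1.5% and 1.9%.

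**Step 4: result for age.** The last column multiplies the standard error by 1.0019 and uses one fewer degree of freedom.

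| R² (assumed) | SE (MME) | SE reduction | Power before cost | Power after cost |
|---|---|---|---|---|
| 0% | 3.07 | none | 90.1% | 90.0% |
| 2% | 3.03 | 1.0% | 90.7% | 90.6% |
| 5% | 2.99 | 2.5% | 91.5% | 91.4% |
| 10% | 2.91 | 5.1% | 92.9% | 92.8% |

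In patients, 266/(1 − R²) − 266 gives about 5, 14 and 30 extra evaluable participants for 2%, 5% and 10%.

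**Step 5: margin in the design.** If 25% of 340 are lost as assumed, 340 × 0.75 = 255 remain, about 127.5 per group, where the same t calculation gives power of 88.9%. There the plan has no spare power, and an R² of 5% from age would bring it to about 90.3% after cost.

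**The case against.** The case against making this change is substantial, and most of it stands.

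- *Nothing is in error.* Under 1:1 randomisation, omitting a prognostic covariate does not bias the difference in means. Chance imbalance is already allowed for in the confidence interval and the type 1 error rate. A reader might infer from the missing term that the primary estimate is compromised; the documents do not support that.
- *Age is not absent from every efficacy model.* A reader might conclude that it is, but SAP 3.4.4 fits the subgroup main effect. Those models estimate effects within subgroups and do not supply the primary comparison, so they do not recover its precision.
- *The gain is not guaranteed.* The R² values are assumptions, and the planned power claims no covariate gain. To call the lost precision free would be too strong: there is a small cost if age explains nothing. At one degree of freedom, though, the break-even is only 0.4% of residual variance.
- *Subgroup status does not show prognostic strength.* Subgroups are chosen to look for effect modification, and the same argument would bring in race/ethnicity and diabetes. This is fair. The case for age rests on its being a collected baseline measure that costs one parameter, not on its being a subgroup factor.
- *Type of operation is not on the same footing.* It has no defined levels and is not named in the baseline list; that it is collected is only implied by the subgroup plan. It needs several parameters, so its break-even is higher.
- *Delirium.* It is tempting to claim that an age imbalance would mislead the delirium comparison. The documents give no relation between age and delirium and no expected delirium rate, so no size can be given from them.

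**Conclusion.** The point holds as an efficiency improvement, not as a flaw in validity. Apart from the subgroup models, the planned efficacy analyses leave out a baseline variable that is already collected and would cost one parameter. Over an assumed R² of 2% to 10%, the primary standard error would fall about 1.0% to 5.1%, and power at 133 per group would rise by roughly 0.5 to 2.7 points after cost. At worst the standard error widens about 0.2%. These figures rest on SD 25 being the residual SD of the current model and on a roughly linear relation with age; the documents do not show where in the range the true value lies. They apply to the linear models. In the logistic and proportional hazards models, adding age also makes the odds ratio or hazard ratio conditional on age, so the benefit there is in power and is not read off as a smaller standard error.

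**What to change.** Before unblinding, amend the SAP to:

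1. Add age as a continuous covariate to the primary ANCOVA in 3.4.1, and so to the analyses that follow the same method (opioid use to discharge, QoR-15, McGill, PROMIS-29).
2. Add age to the pain and delirium models in 3.4.2 and the time-to-event models in 3.4.3.
3. Keep the current covariate set as a named sensitivity analysis.
4. Record that the covariates differ from those in protocol section 7; BMI already does.
5. Add type of operation only if it is recorded for all participants and reduced in advance to a few categories, the same ones as in the subgroup analysis.

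The cost for age is a line of SAP text and one degree of freedom per model, with no new data. With type of operation included, at 4 to 5 extra parameters in total, the worst-case widening of the primary standard error is about 1%. If treatment codes have already been opened, an age-adjusted model should be reported only as a supportive analysis.

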#### Sensitivity Analysis

A sensitivity analysis will jointly model the primary efficacy endpoint with incidence of rescue or intraoperative nerve block, delayed extubation, return to the OR or death during the 72 hours following catheter insertion. The primary endpoint will be analyzed using the ANCOVA model described above, and rescue or intraoperative nerve block, delayed extubation, return to the OR

or death occurrence will be analyzed by logistic regression with the fixed effects used in the ANCOVA model.

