| Statistical Analysis  | Categorical data will be summarized by frequencies and percentages, and continuous variables by means and standard deviations (or medians and interquartile ranges for non-linear data). For the primary analysis, we will perform linear regression, adjusted for sex and intraoperative opioid MME to assess the comparison between trial groups. A modified intention-to-treat analysis will be employed, including only patients who received the block, and excluding patients with prolonged intubation. Sensitivity analyses using complete intention-to-treat and per protocol populations will also be conducted.                                                                                                                                                                                                                                                                                                                                                                                                                                                                                                                                                                                                                                                                                                                                                                                                                                                                                                                                                                                                                                                                                                                                                                                                                                          |

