### *2.2.2 Sample Size Determination*

To detect a mean difference of 10 milligram morphine equivalents (MMEs), assuming a standard deviation of 25 and a 2-sided type 1 error rate of 5%, a sample size of 133 participants per group would be required to provide a power of 90%. Assuming an attrition rate of 25%, approximately 340 patients will need to be randomized.

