## 3.2 Analysis Populations

### 3.2.1 Modified Intent-to-Treat (mITT) Population

The mITT Population will include all randomized participants in whom a block catheter was placed, and a dose of study treatment was administered. Treatment classification will be based on the randomized treatment assignment. The mITT Population will be the primary population used for the efficacy analyses.

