### 3.4.1 *Primary Efficacy Endpoints*

#### Primary Analysis

The primary efficacy endpoint is the cumulative postoperative opioid use measured as MMEs during the 72 hours following catheter insertion. The conversion of different opioids into MMEs will utilize the table provided in the study protocol.

Administered opioids are documented in the CRF on a daily basis; i.e., the date and time of each administered drug is not recorded. In contrast, the date and time of catheter insertion is recorded in the CRF. Consequently, opioid use for each participant will include those that were administered:

- The day of catheter administration
- The two days following the day of catheter administration
- A fraction of the third day following the day of catheter administration. The fraction will depend on the time of day that the catheter was inserted at the beginning of the 72 hour time interval. For example, if 40 MMEs were administered on the 3rd day and the catheter was inserted at 9:00 AM on day 0, the MMEs on the third day that will be included in the primary efficacy analysis would be  $(9/24) \times 40 = 15$  MMEs.

To assess the primary efficacy endpoint, the primary estimand is defined by the following key attributes:

- **Treatment:** 0.2% ropivacaine versus placebo
- **Target Population:** participants who are randomized into the study and received any amount of study treatment
- **Analysis Population:** The mITT Population
- **Intercurrent events:** premature treatment discontinuation, rescue nerve block, death
- **Analysis set and handling of intercurrent events:** Treatment policy strategy will be used. All available MME values during the 72 hours following catheter insertion will be used in the calculation of cumulative postoperative opioid use
- **Population level summary:** The difference in LS mean cumulative postoperative opioid use during the 72 hours following catheter insertion between treatment groups

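### The SAP omits the ITT and per-protocol analyses that the protocol promises, and its one named sensitivity analysis is expected to return essentially the primary estimate

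*Combined protocol and SAP*

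**What the plan says.** **Protocol.** Section 7 states: "Sensitivity analyses using complete intention-to-treat and per protocol populations will also be conducted". The synopsis makes the same commitment. The two places describe the modified ITT set differently. Section 7 requires a catheter and a dose. The synopsis requires receipt of the block and adds "excluding patients with prolonged intubation".

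**SAP populations.** SAP 3.2 defines two sets. The mITT set is "all randomized participants in whom a block catheter was placed, and a dose of study treatment was administered". The Safety set has the same entry rule but classifies patients by treatment received, and it serves safety only. No ITT or per-protocol set is defined, and no reason is given.

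**SAP primary estimand (3.4.1).** The listed intercurrent events are premature treatment discontinuation, rescue nerve block and death. For these, "Treatment policy strategy will be used", and the outcome is the sum of whatever MME values are available in the 72 hours.

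**SAP sensitivity analysis (3.4.1).** "A sensitivity analysis will jointly model the primary efficacy endpoint with incidence of rescue or intraoperative nerve block, delayed extubation, return to the OR"; death completes the list. MME is modelled by the primary ANCOVA, and the events by logistic regression with the same fixed effects. The link between the two parts is not given. SAP 3.4.2 reuses the model for MME to discharge. SAP 3.1.6 rules out imputing missing efficacy data and says that the influence of these events on MME will be explored in the sensitivity analyses. The robust and non-parametric options in 3.4.1 are conditional and address model assumptions only.

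**The concern.** Patients are randomised before surgery (protocol 5.2), and catheters go in after skin closure (synopsis), so some may never be dosed. The promised ITT analysis is what would show whether leaving them out matters. If the SAP is followed, that check and the per-protocol check disappear without explanation.

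The check that remains looks as if it probes the intercurrent events, but it refits the primary ANCOVA on the same patients beside a model for the events. A reader of the results could take close agreement between the two estimates as evidence of robustness, when the agreement is built into the model.

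The event lists also do not match. Premature discontinuation is an intercurrent event in the estimand but is absent from the joint model. Delayed extubation and return to the OR are in the joint model but not in the estimand, and delayed extubation is not defined. Summing available MMEs gives a patient who dies early a low total, which counts as a good outcome, and no analysis treats it otherwise.

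**Working it through.** **1. The plan's own figure.** Inputs (protocol section 7, SAP 2.2.2): difference 10 MME, SD 25, two-sided 5%, power 90%. The normal approximation is n = 2(1.960 + 1.282)² × 25²/10² ≈ 131.3, so 132 per group. With the noncentral t, power is 0.8993 at 132 and 0.9015 at 133. The SAP's statement that "a sample size of 133 participants per group would be required to provide a power of 90"% is therefore reproduced.

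At 25% attrition, 340 randomised leaves 0.75 × 340 = 255 analysed and 85 not. Neither document splits attrition into undosed patients and dosed patients without usable data, so 85 is a ceiling on the undosed.

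**2. What ITT would show.** Let u be the undosed share. Assumptions: 10 MME effect in dosed patients, none in undosed patients, u equal in both arms, SD 25 throughout.

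- ITT difference = 10 × (1 − u)
- ITT power = Φ(10(1 − u)/(25√(2/170)) − 1.96), where 25√(2/170) = 2.71
- mITT power = Φ(10/(25√(2/n)) − 1.96), where n = 170(1 − u)

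| u | Undosed of 340 | ITT difference (MME) | ITT power | mITT power |
|---|---|---|---|---|
| 5% | 17 | 9.5 | 93.9% | 94.9% |
| 10% | 34 | 9.0 | 91.3% | 93.8% |
| 15% | 51 | 8.5 | 88.0% | 92.5% |
| 20% | 68 | 8.0 | 83.9% | 91.0% |
| 25% | 85 | 7.5 | 79.0% | 89.1% |

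**3. Why the joint model tracks the ANCOVA.** Write MME as y = Xβ + σr, and let the log-odds of an event be Xγ + λr, with the same X in both. Given y, the log-odds are X(γ − λβ/σ) + (λ/σ)y. Both bracketed terms are free parameters, so the event part carries no information on β, and the likelihood is maximised at the ANCOVA estimate. A normal random effect shared by the two parts gives the same factorisation, because its distribution given y depends on β only through y − Xβ. With unequal variances by arm, as the SAP specifies, the factorisation is only approximate.

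**4. Simulation.** 266 patients, SD 25, 10 MME effect, about 19% with an event, 20 data sets per scenario. The standard error of the treatment difference is about 3.1 MME. The table gives the joint estimate minus the ANCOVA estimate.

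| Scenario | Mean absolute shift (MME) | Maximum (MME) |
|---|---|---|
| Complete totals, equal variances | 0.00 | 0.00 |
| Complete totals, unequal variances | 0.02 | 0.08 |
| Totals missing in 25% of event patients | 0.37 | 0.91 |
| Totals missing in 50% of event patients | 0.96 | 2.04 |
| Totals missing in all event patients | 1.39 | 6.18 |

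The missing-data scenarios are assumptions and use equal variances. A further 12 data sets with complete totals and equal variances, fitted by numerical integration over a shared random effect, gave unstable shifts (mean absolute 0.95, maximum 6.41 MME). Step 3 makes the true shift zero there, so these are best read as numerical failures. They also show that a shift in the fitted joint model need not mean anything.

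**The case against.** Several stronger readings are tempting, and the documents do not support them.

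- **That the joint model cannot move the estimate.** This needs complete totals and a standard link. The SAP states neither, and step 4 shows movement when totals are missing in event patients. Complete totals are nevertheless the plan's default, because every available value is summed.
- **That intercurrent events go untested.** The estimand names a strategy for them, and the logistic part would describe composite event incidence by arm. What is missing is any alternative handling of MME.
- **That 85 patients will be left out.** This treats all attrition as failure to dose. It is the top of a range.
- **That the primary result is biased.** Participants, the clinical team and operating-room staff are blinded (protocol 3.7), so failure to place a catheter or give a dose should rarely depend on arm. The mITT set also matches the SAP's stated target population. Both arguments stand: no bias in the primary analysis is shown.
- **That an intraoperative block cannot fall in the 72-hour window.** The time phrase may attach only to the later events, and a block given in the OR after insertion is not excluded. The wording is ambiguous.
- **That early deaths distort the result by a known amount.** The documents give no 72-hour death rate, and emergency and unstable patients are excluded, so no size can be attached.

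None of this restores the two promised analyses or makes the joint model a test of how the events are handled.

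**Conclusion.** The point holds in this form. The later SAP leaves out two sensitivity analyses that the current protocol promises, so randomised patients without a catheter or dose appear in no efficacy analysis. Under the assumptions of step 2, ITT would lower a 10 MME difference to between 9.5 MME (17 undosed) and 7.5 MME (85 undosed). This is the size of a missing robustness check and does not show an error in the primary estimate.

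The joint model should return essentially the primary estimate when totals are complete (shift 0 to 0.08 MME against a standard error of about 3.1). It might shift by about 0.4 to 1.4 MME on average if totals are missing in event patients. It therefore does not deliver the exploration announced in SAP 3.1.6, and it does not cover premature discontinuation at all. The conflict over prolonged intubation, which occurs after randomisation and is closely tied to the exploratory endpoint of time to extubation, is a separate inconsistency in how the primary population is described. The primary analysis can stand, but these changes should be made before database lock.

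**What to change.** 1. **SAP 3.2 and 3.4.1.** Add an ITT sensitivity analysis of all randomised patients. State a time origin where no catheter was placed, for example end of surgery, and use it for the third-day fraction as well. Take MME totals from the medication administration record. Add the per-protocol analysis with a defined set, since neither document defines one. If either analysis is to be dropped, give the reason and amend the protocol.
2. **Joint model.** Keep it only as a description of event incidence by arm. State its link, what will be reported from it, and the definition of delayed extubation. Add at least one supplementary analysis that handles death differently from summing available MMEs, such as a composite strategy, so that an early death does not score as low opioid use. Worst ranks for return to the OR are not needed, as it is not an intercurrent event in the estimand. Say how premature discontinuation will be examined.
3. **Intraoperative block.** State whether it precedes insertion. If so, take it out of the 72-hour post-insertion composite.
4. **Synopsis.** Reconcile the prolonged-intubation exclusion with protocol section 7 and SAP 3.2.1, which do not contain it.

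The cost is SAP wording, a few short programs and one protocol correction. The main burden is collecting MME totals for undosed patients, because the documents do not say that these are already captured.

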| Study Intervention    | Subjects will be randomized (1:1) to receive superficial parasternal intercostal plane block with ropivacaine via ultrasound-guided catheter placement or sham block with saline. Catheters will be inserted into the superficial parasternal intercostal plane bilaterally under ultrasound guidance after skin closure. Following initial bolus dosing at the time of catheter placement, a continuous infusion with intermittent boluses every 3-4 hours of 0.2% ropivacaine, or equivalent volume of 0.9% normal saline, will be delivered via catheters for 48 hours post-catheter insertion.                                                                                                                                                                                                                                                                                                                                                                                                                                                                                                                                                                                                                                                                                                                                                                                                                                                                                                                                                                                                                                                                                                                                                                                                                                                                  |

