#### *Visit R: Preoperative Randomization*

- Confirmation of eligibility
- Randomization

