#### Non-Date Values

There will be no imputation of missing efficacy or safety data. However, the potential influence of rescue or intraoperative nerve blocks, delayed extubation, return to OR and death on MME efficacy endpoints will be explored in sensitivity analyses, described below.

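### The joint-model sensitivity analysis counts intraoperative nerve blocks as events after catheter insertion, although a block given in the index operation precedes both the 72-hour window and study drug

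*Combined protocol and SAP*

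**What the plan says.** **Timing.** The study intervention row of the protocol synopsis states: "Catheters will be inserted into the superficial parasternal intercostal plane bilaterally under ultrasound guidance after skin closure". The continuous regimen starts "Following initial bolus dosing at the time of catheter placement". Protocol 5.2 places randomization before surgery ("Preoperative Randomization"). The order is therefore randomization, operation, skin closure, catheter and first bolus, then the 72-hour window.

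**Sensitivity analysis.** SAP 3.4.1 models the primary endpoint jointly with "rescue or intraoperative nerve block, delayed extubation, return to the OR or death during the 72 hours following catheter insertion". Its second sentence repeats the list without a window and makes occurrence of these events a dependent variable: "or death occurrence will be analyzed by logistic regression with the fixed effects used in the ANCOVA model". The model terms are "fixed effects for treatment group, sex, BMI and intraoperative MMEs", the last split at the median. SAP 3.4.2 applies the same joint model to MME until discharge.

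**Purpose.** Under Non-Date Values, SAP 3.1.6 gives the aim of the sensitivity analyses: "the potential influence of rescue or intraoperative nerve blocks, delayed extubation, return to OR and death on MME efficacy endpoints will be explored".

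**Primary estimand.** The listed intercurrent events are "premature treatment discontinuation, rescue nerve block, death", handled by treatment policy.

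No section defines an intraoperative nerve block, gives it a window of its own, or makes it a covariate or a reason for exclusion.

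**The concern.** A block given during the index operation cannot happen in a period that begins once that operation is closed. The programmer has two readings of SAP 3.4.1, and neither does what SAP 3.1.6 promises.

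With the window applied, index-operation blocks never enter the joint model, so their influence on MME is not examined there. With the window ignored, a patient who had such a block counts as having an event, and that event is regressed on a treatment that had not yet started. Rescue blocks and reoperations, which can reflect what happened after dosing, are then mixed with an exposure that cannot.

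The joint model is the only analysis the SAP names for the influence of nerve blocks on the MME results. If its event variable combines pre-dose and post-dose occurrences, its result is hard to interpret for either MME endpoint.

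**Working it through.** **1. Order of events**

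| Step | Source | Relation to first dose |
|---|---|---|
| Randomization | Protocol 5.2, Visit R | before |
| Index operation, with any intraoperative block | Protocol synopsis | before |
| Skin closure, catheter, initial bolus | Protocol synopsis | time zero |
| 72-hour window for the joint-model events | SAP 3.4.1 | after |

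An index-operation block is thus after randomization but before study drug. SAP 3.1.3 generally defines baseline as the last value before the first dose, so by the SAP's own convention the block is a pre-dose characteristic. SAP 3.4.1 already treats the parallel intraoperative exposure, opioid MMEs, as a covariate.

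**2. The plan's own figure**

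Inputs from SAP 2.2.2: difference 10 MME, SD 25 (variance 625), two-sided 5%, power 90%.

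n per group = 2 × (1.960 + 1.282)² × 625 / 10² = 131.4, rounded up to 132. The t-test version gives 132.3, rounded up to 133. The stated 133 per group reproduces and does not depend on how intraoperative blocks are handled.

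**3. Size of the omitted exposure**

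The documents give no block frequency and no effect on MME. Assumed ranges: share of patients q = 5–20%, effect d = 5–20 MME, the same in both arms.

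Share of the assumed variance = q(1 − q)d² / 625:

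| q | d = 5 | d = 10 | d = 20 |
|---|---|---|---|
| 5% | 1.19/625 = 0.2% | 4.75/625 = 0.8% | 19/625 = 3.0% |
| 10% | 2.25/625 = 0.4% | 9/625 = 1.4% | 36/625 = 5.8% |
| 20% | 4/625 = 0.6% | 16/625 = 2.6% | 64/625 = 10.2% |

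The right-hand column assumes an effect twice the 10 MME that the trial is powered to detect, so it is generous.

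**4. Chance imbalance in the primary analysis**

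95% range of the shift in the treatment difference = ±1.96 × √(2q(1 − q)/133) × d:

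- q = 5%, d = 5: 1.96 × 0.0267 × 5 = ±0.26 MME
- q = 10%, d = 10: 1.96 × 0.0368 × 10 = ±0.72 MME
- q = 20%, d = 20: 1.96 × 0.0491 × 20 = ±1.92 MME

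For scale, the planned analysis has a standard error of 25 × √(2/133) = 3.07 MME, a 95% half-width of about 6.0 MME. If the SD of 25 already reflects block-to-block variation, this chance component is part of that uncertainty and not an addition to it.

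**The case against.** **The wording may be loose, not wrong.** The 72-hour phrase might qualify only the last items of the list, and the term might mean a block at a return to the OR. Either is possible, but neither is stated. Return to the OR is a separate item in the same list, and the narrow meaning would leave index-operation blocks without any handling. These blocks might still appear in the concomitant-medication summary (SAP 3.3.4) if they are collected, but a summary does not explore their influence on MME.

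**A reader might infer that the treatment odds ratio for rescue or complications is diluted.** The arithmetic is simple. With assumed event risks of 10% versus 20% (odds ratio 0.44) and blocks in 10% of each arm, the pooled risks are 1 − 0.9 × 0.9 = 19% and 1 − 0.8 × 0.9 = 28%, an odds ratio of 0.60. But the SAP does not promise an odds ratio from this model, as it does for delirium, and does not say that the events form one composite. Its stated interest is MME. This shift is therefore not a demonstrated harm.

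**A reader might infer that such a block acts on the same nerves as the study block and lowers opioid use in both arms.** The documents give no type, site, agent or frequency, so this is unsupported.

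**A reader might infer that the estimand is defective because it names rescue block only.** A pre-dose block is not an event after treatment start, so its absence from that list is consistent. The list also omits delayed extubation and return to the OR.

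**Adjustment conditions on something that happened after randomization.** True. However, the block precedes study drug and the clinical team is blinded (Protocol 3.7), so adjusting for it or leaving these patients out introduces no expected bias.

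**Conclusion.** The point stands as a defect of one planned sensitivity analysis, used for 72-hour MME and for MME to discharge. Taken literally, SAP 3.4.1 misses index-operation blocks; taken loosely, it treats a pre-dose exposure as an outcome of treatment. Either way the aim stated in SAP 3.1.6 is not properly met.

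The primary ANCOVA is not biased by this, because study drug cannot have influenced a block given before it under blinding. The sample size is unaffected. Under the assumed 5–20% frequency and 5–20 MME effect, the exposure accounts for roughly 0.2–10% of the assumed variance, and chance imbalance amounts to about ±0.3 to ±1.9 MME. Those ranges are assumptions; the true size depends on how often such blocks were given, which the documents do not say. The post-skin-closure timing rests on the protocol synopsis; the catheter and administration text in Protocol 3.6 does not contradict it. The change is worth making before database lock, but the trial's main result does not hinge on it.

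**What to change.** In SAP 3.4.1:

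- Limit the joint-model events to those after catheter insertion: rescue block (including any block at a return to the OR), delayed extubation, return to the OR, and death. The same restriction then carries over to MME until discharge in SAP 3.4.2.
- Define index-operation nerve block (yes/no) as a pre-dose characteristic and tabulate it by arm.
- Add it as a covariate in a sensitivity version of the ANCOVA, and repeat the analysis without these patients.

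Bring the wording of SAP 3.1.6 into line, so that it points to these analyses for intraoperative blocks and to the joint model for post-insertion events.

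The cost is a few lines of text before lock, one table row and one or two extra model runs. The SAP already presumes that the block is recorded, since it plans to model it; this should be confirmed against the CRF. The primary analysis stays as it is.
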